#### Approach to Analysis

Before developing statistical models, an examination of the univariate distribution of variables will be conducted (eg, scatter plots). Statistics, such as means or proportions, standard errors, ranges, and estimates of skewness and kurtosis will be derived for the overall samples and stratified by condition and characteristics of small businesses and YPAOs using SAS 9.4 and used as guidelines in the application of both bivariate and multivariate analyses [85]. Data transformation procedures (eg, logarithmic) may be applied to quantitative variables whose distribution shows considerable departure from normality. In the case of discrete variables, results will provide guidance in recoding these variables appropriately for statistical modeling. Graphical data will be developed to provide visual comparisons of changes across time between the 2 study conditions on key measures of small business involvement and YPAO utilization by the youth. The primary outcome will be examined using a mixed-model, nested logistic regression analysis of proportions where (1) businesses are nested in neighborhoods and (2) neighborhoods are treated as a nested random effect within treatment conditions. Generalized models will be used to explore potential mediators/moderators of outcomes. For example, a model will be constructed with experimental condition (treatment vs control), neighborhood variables (eg, median income), and business variables (eg, number of employees and years in business) as the independent variables and mean percent change in small businesses donating as the dependent variable. In another model, donation amounts equated to US dollars will be used as the dependent variable. To accommodate the complex nature of the research design, the SAS PROC GLIMMIX and SAS PROC MIXED (SAS, 2015) procedures will be used.

### Sample Size Determination for Aim 3

The primary outcome for aim 3 will be the percent increase in youth participants from baseline to follow-up. We hypothesize that the increase will be significantly greater at YPAOs in the treatment neighborhoods receiving support from small businesses than at YPAOs in the control neighborhoods. Previously in low-income, minority neighborhoods, we found an average of 46.7 (SD 37) youths participating in YPAOs [52,90]. With the proposed sample size of 10 neighborhoods per condition from aim 2, our pilot parameter estimates, an ICC of 0.05, and a desired power of at least 80%, we would need 35 YPAO assessments per condition to detect a difference of 0.5 percentage points between conditions at posttest. We expect a total of 140 YPAOs in our 20 study neighborhoods with 20% (28/140) being eligible for SOPARC assessments [52]. Given a 15% to 17% attrition rate and a response rate of 60%, we will randomly select 90 YPAOs for interviews to yield 44 YPAOs with baseline and follow-up data from the survey. These will be combined with the 28 YPAOs observed, giving a total of 70.

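### Aim 3 sample size: 35 YPAOs per condition cannot detect 0.5 percentage points; on the stated inputs the detectable difference is about 100 times larger

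*Protocol article*

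**What the plan says.** The section Sample Size Determination for Aim 3 defines the endpoint: "The primary outcome for aim 3 will be the percent increase in youth participants from baseline to follow-up". The only distributional figures it gives are cross-sectional: "we found an average of 46.7 (SD 37) youths participating in YPAOs". It then lists the other inputs, with a power target of 80% or more: "With the proposed sample size of 10 neighborhoods per condition from aim 2, our pilot parameter estimates, an ICC of 0.05, and a desired power". From these it concludes that "we would need 35 YPAO assessments per condition to detect a difference of 0.5 percentage points between conditions at posttest". The planned yield matches that number: after the surveyed YPAOs are counted, "These will be combined with the 28 YPAOs observed, giving a total of 70", which is 35 per condition. Alpha, sidedness, the SD of the percent change and any baseline/follow-up correlation are not given. The hypothesis is worded in one direction: "We hypothesize that the increase will be significantly greater at YPAOs in the treatment neighborhoods receiving support from small businesses".

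**The concern.** The endpoint is a percent increase, so a difference of 0.5 percentage points means, for example, a 10.5% increase against a 10.0% increase. On a mean of 46.7 that is about a quarter of one youth per YPAO, set against an SD of 37. Seventy YPAOs in 20 neighborhoods cannot resolve that. The Power Analysis section uses percentage points in the ordinary sense (27% against 8% is given as 19 percentage points), so a reader will take the aim 3 statement the same way.

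This is the stated sensitivity of the aim 3 primary outcome and of hypothesis 3. Taken at face value, a null result would seem to exclude all but negligible effects on utilization, and anyone planning a later study from this sentence would start from a sensitivity that is about 100 times too favourable.

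**Working it through.** **Inputs from the article:** mean 46.7; SD 37; ICC 0.05; 10 neighborhoods per condition; 35 YPAOs per condition; power 80%.

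**Assumed, because not stated:** alpha 0.05, tried one-sided and two-sided; normal approximation; percent differences expressed relative to the mean of 46.7.

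**Clustering.** YPAOs per neighborhood: 35/10 = 3.5. Design effect: 1 + (3.5 − 1) × 0.05 = 1.125. Effective n per condition: 35/1.125 = 31.1. Standard error of the difference: 37 × √(2/31.1) = 9.38 youths.

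**1. The plan's claim as printed.** 0.5 percentage points = 0.005 × 46.7 = 0.23 youths, or 0.23/9.38 = 0.025 standard errors.
- Power, one-sided: Φ(−1.645 + 0.025) = 5.3%.
- Power, two-sided: 2.6% in the favourable direction, about 5% counting both tails.
- Required n before any design effect: about 310,000 (one-sided) or 394,000 (two-sided) per condition.
- With 10 neighborhoods per condition and ICC 0.05, no number of YPAOs is enough. As n grows without limit, the unadjusted detectable difference falls only to (z_α + z_β) × 37 × √(2 × 0.05/10), which is 20% (one-sided) or 22% (two-sided) of the mean.

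The printed claim does not reproduce.

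**2. What 35 per condition detects at posttest, unadjusted.**
- One-sided 5%: (1.645 + 0.842) × 9.38 = 23.3 youths = 49.9% of 46.7.
- Two-sided 5%: (1.960 + 0.842) × 9.38 = 26.3 youths = 56.3% of 46.7.
- With t on 18 df: 24.4 youths (52%) or 27.8 youths (60%).

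Ratio to the stated 0.5 points: 49.9/0.5 = 100 (one-sided) or 56.3/0.5 = 113 (two-sided).

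**3. Crediting baseline adjustment.** Multiply by √(1 − r²), where r is the baseline/follow-up correlation. Two-sided:

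| r | Detectable difference, % of mean |
|---|---|
| 0 | 56 |
| 0.46 | 50 |
| 0.7 | 40 |
| 0.8 | 34 |
| 0.9 | 25 |
| 0.99 | 8 |

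To reach 0.5 points the residual SD would have to be about 0.33 youths (two-sided) or 0.37 (one-sided) instead of 37, a correlation above 0.9999.

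**4. Other readings of 0.5.**
- *0.5 SD:* needs 63 (one-sided) or 87 (two-sided) per condition; power at 35 is 63% or 50%.
- *0.5 youths:* needs about 68,000 or 86,000 per condition before any design effect.
- *0.5 as a proportion (50% of 46.7 = 23.35 youths):* let n₀ be the required n without clustering. Solving n = n₀ × [1 + (n/10 − 1) × 0.05] gives n = 0.95 n₀/(1 − 0.005 n₀).
  - One-sided, unadjusted: n₀ = 31.05, n = 34.9, so 35.
  - Two-sided, unadjusted: n₀ = 39.42, n = 46.6, so 47.
  - Two-sided with r = 0.46: n₀ = 39.42 × (1 − 0.46²) = 31.08, n = 34.95, so 35.

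The figure of 35 is therefore recovered for a 50% relative difference in at least two ordinary ways.

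**The case against.** The strongest objection is that the endpoint is change from baseline while the calculation above uses a cross-sectional SD. The article refers to "our pilot parameter estimates", which may include more than the printed mean and SD, and a full protocol may hold alpha, sidedness and a correlation. This part stands: the exact detectable difference is not fixed by the article, and 56% is not the only candidate. It does not rescue 0.5 points, because the gap is about 100-fold and even r = 0.99 leaves about 8%.

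A second objection is that this is a slip of units in a pilot study: if 50% was meant, the sample size is sound. That is plausible and would make the repair trivial, but it remains an inference, and the printed sentence is still false.

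Three stronger readings are tempting and are not supported:
- *An undeclared one-sided test must lie behind the 35.* A two-sided test with r of about 0.46 gives the same number. The directional hypothesis does not settle sidedness.
- *The study can see only changes of half the mean or more.* That assumes no baseline adjustment. At r = 0.7 the two-sided figure is about 40%, and power for a 50% difference is about 94%.
- *Aim 3 is underpowered for its intended effect.* Two-sided power for a 50% difference is 70% only if unadjusted, and 80% at r = 0.46. The article does not say which applies, or that 50% was intended.

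**Conclusion.** The stated sensitivity for aim 3 is wrong by about two orders of magnitude, in the favourable direction. This conclusion holds for either sidedness, with or without the design effect (without it, 47% or 53% of the mean), and for any plausible baseline correlation. What replaces 0.5 points is conditional on what the article does not give: about 50% of the mean (one-sided) or 56% (two-sided) without adjustment, and less with adjustment. These figures also rest on taking SD 37 relative to mean 46.7 as the scale for the percent change, since its own SD is not given. The error lies in the effect size reported. It does not show that the design or the number of YPAOs is wrong.

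**What to change.** Replace 0.5 percentage points with the difference the design can detect, and state alpha, sidedness and the assumed baseline/follow-up correlation beside it. Only the investigators can say which case applies:
- two-sided 5%, no baseline adjustment: about 26 youths, 56% of the mean of 46.7;
- one-sided 5%, no baseline adjustment: about 23 youths, 50%, with the one-sided test declared;
- two-sided 5%, baseline-adjusted: 50% if r is about 0.46, or the corresponding figure for another justified r (40% at r = 0.7).

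Do not describe the aim 3 comparison, here or when results are reported, as sensitive to differences below one percent. The cost is one sentence and a less favourable stated sensitivity. Sample, design and data collection stay as they are.

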#### Youth Physical Activity Opportunity Provider Surveys

In-person interviews were conducted by trained personnel with a randomly selected sample of 44 YPAO providers. Our reliable YPAO survey was used to gather detailed information on the YPAO including the number of youth participants, descriptions of all features and amenities, programmatic information (eg, fees, operating times, and sessions per week), personnel qualifications, and start-up and operating costs including how costs were covered [52]. If a small business providing a YPAO was selected for the survey, we completed the YPAO survey with them in addition to the small business survey.

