## Results

The study protocol was approved by our institutional review board on July 13, 2018. All preparatory activities (eg, hiring, training, and data collection procedures finalized) were completed on 31 October 2018. In addition, 20 study neighborhoods comprising 53 US census block groups meeting the inclusion criteria were identified and randomly assigned to treatment or control conditions (Multimedia Appendix 6). A total of 9 focus groups were completed with members from the study neighborhoods who were small business owners, YPAO providers, or parents and guardians. Recruitment was accomplished in a number of different ways—requests made at events (eg, business chamber meeting), business chamber networking, direct contact (eg, email, phone, and site visits), ad placements, and active recruitment at community locations. Focus group data have been transcribed and are currently being analyzed. It will be utilized in May 2019 to revise any components of the intervention and expected results will be published in fall 2019.

In December 2018, a database containing the names, addresses, and geolocations (eg, US census block group) of the 87,982 businesses currently licensed in Delaware was obtained from the Delaware Department of Finance: Division of Revenue. The database was edited to include only small businesses with a physical, nonresidential address located in 1 of our 20 study neighborhoods. During May and June, 2019, baseline surveys were completed with 244 owners and managers of small businesses in the study neighborhoods. Data from small businesses will be analyzed in July 2019 and results will be disseminated in August 2019. In addition, a total of 96 YPAOs were identified in the 20 study neighborhoods, and interviews have been conducted with 35 nonpark YPAOs from May 6 to June, 2019. The park YPAOs (n=27) were examined in June, 2019 using the SOPARC and PARA methods to determine usages and presence/absence of amenities.

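### Aim 3 plans for 70 YPAOs with paired data, but either of the article's two baseline interview counts falls short of 70 once the plan's own attrition is applied

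*Protocol article*

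**What the plan says.** Under Sample Size Determination for Aim 3, the article states the requirement as follows: "we would need 35 YPAO assessments per condition to detect a difference of 0.5 percentage points between conditions at posttest". The power sought is at least 80%, with 10 neighborhoods per condition and an ICC of 0.05.

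The same paragraph explains how the number will be reached. It starts from a frame: "We expect a total of 140 YPAOs in our 20 study neighborhoods", of which 28 are to be observed with SOPARC. A further 90 are to be selected for interview. With 60% response and 15% to 17% attrition, these should leave 44 with both assessments. The paragraph ends: "These will be combined with the 28 YPAOs observed, giving a total of 70".

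Two other places report what was obtained at baseline:

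- Youth Physical Activity Opportunity Provider Surveys (Methods): "In-person interviews were conducted by trained personnel with a randomly selected sample of 44 YPAO providers".
- Results: "a total of 96 YPAOs were identified in the 20 study neighborhoods, and interviews have been conducted with 35 nonpark YPAOs". The next sentence there gives 27 parks observed.

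Procedures for Aim 2 and the Discussion both describe the baseline work as finished in June 2019.

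**The concern.** The aim 3 paragraph still rests on planning assumptions that the article's own Results have overtaken. The frame is 96 YPAOs, not 140. The number of interviews is given twice with different values, and no passage explains the difference. One of those values, 44, is also the number that the plan expected to keep after attrition, so it may be an achieved baseline count or a planning figure carried over. The text does not show which.

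Aim 3 has its own primary outcome, a percent change from baseline, and its own significance hypothesis. Only YPAOs with a baseline value can contribute, so the baseline count caps the analysable sample. A reader who relies on the paragraph would believe that 35 per condition and 80% power are still expected.

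**Working it through.** **Inputs from the article**

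- Required: 35 per condition, 70 in total (Sample Size Determination for Aim 3).
- Planned: 140 YPAOs, 90 selected, 60% response, 15% to 17% attrition, 44 paired interviews, 28 observed (same section).
- Found: 96 YPAOs, 27 parks, 35 nonpark interviews (Results).
- Conflicting interview count: 44 providers (Provider Surveys section).

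**1. The plan's own yield**

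90 × 0.60 × 0.83 = 44.8 and 90 × 0.60 × 0.85 = 45.9. The stated 44 is close to this. Attrition is therefore applied to the interviews, and the 28 observed sites are carried over in full. The sum is 44 + 28 = 72, not 70. This is a small slip that understates the planned yield.

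**2. The frame**

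96 − 27 = 69 nonpark YPAOs. If interviews are for nonpark sites, as the addition of the two groups implies, 90 cannot be drawn from 69. At the plan's rates, 69 × 0.60 × 0.83 to 0.85 = 34.4 to 35.2. Adding 27 parks gives 61.4 to 62.2, below 70.

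**3. The paired sample on each reported count (attrition on interviews only, as in the plan)**

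| Interviews | Baseline total | Interviews kept (× 0.83 to 0.85) | Plus 27 parks | Per condition, even split |
|---|---|---|---|---|
| 35 (Results) | 35 + 27 = 62 | 29.1 to 29.8 | 56.1 to 56.8 | about 28 |
| 44 (Provider Surveys) | 44 + 27 = 71 | 36.5 to 37.4 | 63.5 to 64.4 | about 32 |

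The first row is below 70 before any loss. The second is above 70 at baseline by one YPAO and falls below it under the stated attrition. If parks were lost at the same rate, the totals would be 62 × 0.83 to 0.85 = 51.5 to 52.7 and 71 × 0.83 to 0.85 = 58.9 to 60.4.

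**4. What this could mean for power (illustration only)**

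The article gives no alpha, no sidedness and no SD for the percent change. One set of assumptions reproduces its figure:

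- the difference is 50% of the mean count, 0.5 × 46.7 = 23.35 youths;
- the SD is 37, from "we found an average of 46.7 (SD 37) youths participating in YPAOs";
- alpha is one-sided 0.05;
- arms are equal in size;
- the design effect is 1 + (n/10 − 1) × 0.05, for n YPAOs per condition in 10 neighborhoods.

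Power = Φ[(23.35/37) × √(n_eff/2) − 1.645], where n_eff = n / design effect.

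| n per condition | Design effect | n_eff | Power |
|---|---|---|---|
| 35 (plan) | 1.125 | 31.1 | 80.1% |
| 32 (44 interviews) | 1.11 | 28.8 | 77.4% |
| 28 (35 interviews) | 1.09 | 25.7 | 73.1% |

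On these inputs 35 is the smallest n that reaches 80%, so the plan's figure is reproduced with no margin for loss.

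**The case against.** **The two counts may not measure the same thing.** One is of providers and the other of nonpark YPAOs, and the nine extra providers could run parks. That is possible, but the article does not say so. On that reading the extra interviews would add no new sites beyond the 27 parks already counted, and the total would return to 62.

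**The 90 were not expressly limited to nonpark sites.** This is correct, and the frame argument in step 2 is to that extent an inference. The attrition result in step 3 does not depend on it.

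**The calculation was made in advance, and under-recruitment is not a planning error.** The required 35 per condition is indeed not made wrong by a smaller frame. What no longer holds is the expected yield, printed beside achieved counts that contradict it.

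**New YPAOs will be tracked.** They have no baseline value, so they cannot enter a percent change from baseline.

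**A stronger reading is tempting but not supported.** A reader might infer that the baseline is settled at 62 and that 80% power cannot be met. The 62 rests on the Results alone; the Methods count gives 71 before attrition. Power cannot be fixed either. The effect is written as 0.5 percentage points, and taken literally it does not reproduce 35 per condition. The hypothesis is directional ("the increase will be significantly greater at YPAOs in the treatment neighborhoods receiving support from small businesses"), but no one-sided test is declared. With the same inputs at two-sided 0.05, 47 per condition would be needed, so two-sided figures would not measure a loss from the stated 80%.

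**This is a pilot, and the aim 2 primary outcome is untouched.** That stands and limits the weight of the point.

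**Conclusion.** The point holds as an inconsistency in the aim 3 sample size. The article reports 44 interviews in one place and 35 in another, and under the plan's own 15% to 17% attrition on interviews both leave fewer than 70 paired YPAOs: about 64 or about 56 to 57. The shortfall is therefore roughly 6 to 14 YPAOs. This conclusion needs only the article's counts and rates, and the plan's practice of carrying observed parks over without loss.

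The effect on power is less certain. On the unstated assumptions that reproduce the plan's 35 per condition, power would be about 77% at 32 per condition and about 73% at 28. These are illustrations, not a finding that the trial has a particular power. The size is moderate and confined to aim 3.

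**What to change.** - Reconcile the 44 in the Provider Surveys section with the 35 in the Results. If they count different units, say so and give the number of distinct YPAOs with a baseline assessment.
- In Sample Size Determination for Aim 3, put the observed counts (96 identified, 27 parks, the true interview number) beside or in place of the expected 140, 90 and 28.
- Correct the planned sum: 44 + 28 is 72.
- Restate the expected paired sample, about 56 to 57 or about 64 depending on the reconciled count, with the resulting power or detectable difference. State the alpha, sidedness, effect and SD used.

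The cost is the rewording of one paragraph, one corrected count and a short recalculation. No design element changes. The stated power will probably look less favourable. Follow-up is scheduled for July to August 2020, so the correction can be made before outcome data exist.

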### Potential Problems and Solutions

#### Attrition and Evaluation of Missing Data

Over the past 2 decades, our research team has developed methods to ensure low rates of missing data in our projects. One aspect of this study most likely to result in missing data is the longitudinal assessment of businesses/YPAOs. We will attempt to minimize missing data by maintaining contact with study businesses/YPAO providers and if dropout does occur, we will attempt to determine the reasons why and how much of their study participation was affected. We will examine characteristics associated with attrition and adjust models for attrition and/or baseline group differences.

#### Appealing to Small Businesses

We have been successful in the past in obtaining information from small businesses and soliciting their support for community physical activity initiatives. In the proposed study, we expect to elicit significant increases in support for YPAOs from small businesses in the treatment neighborhoods because the intervention contains numerous components that stimulate donations from small businesses.

#### Measuring Youth Physical Activity Opportunity Utilization

We do not foresee a problem recruiting YPAO providers to participate in the study. We were successful at obtaining detailed information from YPAO providers in a previous study and, in the proposed study, they will receive compensation for their participation and have the opportunity to receive donated funds [52].

## Results

The study protocol was approved by our institutional review board on July 13, 2018. All preparatory activities (eg, hiring, training, and data collection procedures finalized) were completed on 31 October 2018. In addition, 20 study neighborhoods comprising 53 US census block groups meeting the inclusion criteria were identified and randomly assigned to treatment or control conditions (Multimedia Appendix 6). A total of 9 focus groups were completed with members from the study neighborhoods who were small business owners, YPAO providers, or parents and guardians. Recruitment was accomplished in a number of different ways—requests made at events (eg, business chamber meeting), business chamber networking, direct contact (eg, email, phone, and site visits), ad placements, and active recruitment at community locations. Focus group data have been transcribed and are currently being analyzed. It will be utilized in May 2019 to revise any components of the intervention and expected results will be published in fall 2019.

In December 2018, a database containing the names, addresses, and geolocations (eg, US census block group) of the 87,982 businesses currently licensed in Delaware was obtained from the Delaware Department of Finance: Division of Revenue. The database was edited to include only small businesses with a physical, nonresidential address located in 1 of our 20 study neighborhoods. During May and June, 2019, baseline surveys were completed with 244 owners and managers of small businesses in the study neighborhoods. Data from small businesses will be analyzed in July 2019 and results will be disseminated in August 2019. In addition, a total of 96 YPAOs were identified in the 20 study neighborhoods, and interviews have been conducted with 35 nonpark YPAOs from May 6 to June, 2019. The park YPAOs (n=27) were examined in June, 2019 using the SOPARC and PARA methods to determine usages and presence/absence of amenities.

